## Abstract

**Background:**

The clinical inability to correctly identify late fetal growth restriction (FGR) within a group of fetuses who are identified as small for gestational age (SGA) is an everyday problem for all obstetrician-gynecologists. This leads to substantial overtreatment of healthy small fetuses but also inadequate detection of the growth-restricted fetuses that may benefit from timely delivery. Redistribution of the fetal circulation, signaled by an abnormal ratio of the Doppler velocity flow profiles of the umbilical artery and the middle cerebral artery, more specifically an increased umbilicocerebral ratio (UCR) (or its inverse: a decreased cerebroplacental ratio (CPR)), is an adaptation to chronic hypoxemia and nutritional scarcity with long-term consequences in survivors. The relevance of an abnormal UCR has been signaled extensively, and there is a general consensus that it is a signal of FGR, independent of size, with a strong association with poor outcomes. Yet, in the current literature, no comparisons of a monitoring-delivery strategy based on unfavorable UCR have been published. The objective of the Doppler Ratio In fetal Growth restriction Intervention Trial At (near) Term (DRIGITAT) is to evaluate if the timing of the delivery based on an abnormal UCR in late preterm fetuses identified as SGA improves neurodevelopmental outcomes at 2 years of age.

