#### Relevant concomitant care permitted or prohibited during the trial {11d}

The DRIGITAT protocol allows centers to provide their usual care according to local protocol. All other care deemed clinically necessary is allowed. The minimum required procedures and assessments that participants must undergo are described below. Most of these procedures and assessments are already embedded in local protocols on FGR of participating hospitals.Cardiotocography: CTG monitoring takes place in all fetuses with an abnormal UCR with a frequency as indicated by local protocol. The study protocol advises CTG monitoring at least twice a week in case of abnormal UCR.Ultrasound investigation: the study protocol recommends to perform a weekly ultrasound scan on all participants. The ultrasounds will be performed by trained personnel.Fetal biometry: routine fetal biometry measurements according to the departmental protocol should take place every 10–14 days.Fetal and maternal Doppler measurements: fetal Doppler measurements should be done on a weekly basis. At each visit, multiple Doppler measurements are taken, and the measurement of best quality is used. This is usually the PI of the lowest value. When the UCR is > 0.8 for the first time, Doppler measurements should be repeated to confirm the abnormal UCR. Ideally, the measurement is repeated the next day, with a minimum interval of 15 h. Randomization can take place when the UCR is abnormal on two different occasions with at least one day (a minimum of 15 h) in between.Middle cerebral artery (MCA) Doppler measurement: Doppler blood flow waveforms should be measured in the middle cerebral artery just past the level of the bifurcation of the internal carotid artery [21].Umbilical artery (UmbA) Doppler measurement: Doppler blood flow velocity waveforms should be measured in the umbilical artery in a free-floating loop of the mid-section of the umbilical cord [22].Uterine artery (UtA): Doppler blood flow waveforms should be measured in the uterine artery, ideally 1 cm downstream from the crossover point with the external iliac artery [23].Amniotic fluid measurements: amniotic fluid index (AFI) or the single deepest vertical amniotic fluid pocket (SDP) should be measured.Maternal surveillance: standard maternal surveillance will include, at least, the measurement of blood pressure and, if abnormal, a check for proteinuria.Placental pathology: we advise all hospitals to send the placenta to their own pathology department for histopathologic investigation according to national consensus protocol [24].

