#### Sample size {14}

The primary outcome is a clinically relevant difference of 7 points on the Bayley-III scale [25]. With a standard deviation of 15 points in both treatment groups, an alpha of 0.05 and a desired power of 80% for a two-sample *t-*test, 74 patients need to be recruited in each arm of the nested RCT. Accounting for a 20% loss to follow-up of randomized fetuses, 185 women will be needed for the RCT in total. Assuming a 20% incidence of abnormal UCR within the cohort of SGA fetuses and accounting for an inclusion rate in the trial of 60% we calculate to need a cohort of 1542 patients. Despite the fact that we have a history of very low rates of loss to follow-up in our RCTs, we calculate 20% loss to follow-up of randomized fetuses because of the long interval (2 years) before assessment for the primary outcomes.

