### Assignment of interventions: allocation

#### Sequence generation {16a}

The allocation sequence is computer-generated using the online randomization service of Castor EDC (Castor Electronic Data Capture. 2019 [online] available at https://castoredc.com.). Randomization will be done using variable block sizes of 4 and 6, and will be stratified by gestational age (dichotomous; before or after 36 weeks) and participating hospital.

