## Statistical methods

### Statistical methods for primary and secondary outcomes {20a}

Principal analyses will be performed on an intention-to-treat basis. The primary analysis will compare mean Bayley-III scores at 2 years and test the difference using a linear regression model controlling for the stratification factor. If women with suspected FGR (UCR > 0.8 or CPR < 1.25) allocated to the intervention group (timely delivery) have toddlers with better Bayley scores at 2 years, it will be concluded that timely delivery is beneficial based on UCR classification.

A sample of children born in the cohort will also be invited for Bailey-III testing and other outcomes assessed at 2 years of age. A sampling of patients from the cohort will be done against the index date of the trial patient.

Secondary endpoints will be analyzed as relative risks or differences in means with 95% confidence intervals. The chi-square tests and *t*-tests will be used for parametric dichotomous and continuous outcomes respectively. The Mann-Whitney tests with a median difference in medians (Hodges-Lehmann estimate) will be used for non-parametric continuous outcomes.

Data on pregnancy and short-term outcomes are expected only to be missing if patients withdraw consent. Long-term outcomes are anticipated to be missing in up to 15% of patients. The primary outcome will be assessed on a complete case analysis, with sensitivity analysis using multiple imputation.

An alpha of 0.05 is considered for statistical significance.

Data from the cohort study will be used as a comparator group to evaluate the course of all pregnancies, irrespective of UCR/CPR value, and inform whether different UCR/CPR thresholds or combination with other (serum) markers should be considered.

Statistical analyses will be conducted using the latest version of SPSS (SPSS Chicago, IL, USA).

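### Adding the continuous UCR at randomisation to the primary model would be a low-cost, probably small gain in precision; the planned analysis is valid without it

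*Protocol article*

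**What the plan says.** Under Statistical methods for primary and secondary outcomes {20a}, the primary analysis is by intention to treat. It tests the difference in mean scores "using a linear regression model controlling for the stratification factor". No further covariate is named. Under Sequence generation {16a}, randomisation "will be stratified by gestational age (dichotomous; before or after 36 weeks) and participating hospital"; UCR is not among these factors.

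UCR is known before allocation. Eligibility criteria {10} requires a value above 0.8 on at least two occasions, and section {11d} repeats this: "Randomization can take place when the UCR is abnormal on two different occasions". The Abstract (Background) describes an abnormal UCR as "a signal of FGR, independent of size, with a strong association with poor outcomes".

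Other uses of numeric Doppler data are exploratory. Section {20a} will use cohort data to consider other UCR/CPR thresholds, and section {20b} plans hypothesis-generating subgroup analyses by the components of UCR.

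The sample size in section {14} rests on an unadjusted two-sample t-test: "With a standard deviation of 15 points in both treatment groups, an alpha of 0.05 and a desired power of 80" per cent, so that "74 patients need to be recruited in each arm of the nested RCT".

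**The concern.** In a randomised comparison of means, a baseline variable that predicts the outcome can be put in the model to reduce residual variance and to remove the effect of a chance imbalance in that variable. The trial measures such a candidate on every randomised woman, treats it as prognostic when abnormal, and uses it in the RCT as an entry threshold and, through its components, for exploratory subgroups. Leaving its numeric value out of the confirmatory model may give up some precision at a sample size set for 80% power. If investigators wished to adjust for UCR after seeing the results, the choice would look data-driven, so it is best made beforehand.

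**Working it through.** **Inputs from section {14}:** difference 7 points, SD 15 in both arms, alpha 0.05 (two-sided assumed; the article does not say), power 80%, 74 per arm, 20% loss to follow-up, 185 in total, 20% of the cohort with abnormal UCR. **Input not in the article:** the correlation r between UCR at randomisation and Bayley-III score among randomised women. It is assumed below.

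1. *Reproducing the plan.* A two-sided two-sample t-test with standardised difference 7/15 needs 73.05 per arm, rounded up to 74. Then 2 × 74 / (1 − 0.20) = 185. Both stated figures reproduce. Power at 74 per arm is 80.5%, with no covariate needed.

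2. *Effect of adjustment.* Adding one continuous covariate changes the residual SD to 15 × √(1 − r²). The half-width of the 95% interval is 1.96 × SD × √(2/74).

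| Assumed r | Residual SD | Power at 74 per arm | 95% CI half-width (points) |
|---|---|---|---|
| 0 | 15.00 | 80.5% | 4.83 |
| 0.1 | 14.92 | 80.9% | 4.81 |
| 0.2 | 14.70 | 82.1% | 4.74 |
| 0.3 | 14.31 | 84.0% | 4.61 |

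3. *Cost of adjustment.* The table ignores the price of estimating the covariate's slope. Chance correlation between covariate and arm inflates the variance by about 1/(N − 4) = 1/144 = 0.7% at N = 148. Gain and cost balance when (1 − r²)(1 + 1/144) = 1, so r² = 1/145 and r = 0.083. Below that value adjustment gains nothing. At r = 0, power falls from 80.5% to 80.2%.

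4. *Truncation at 0.8.* As an illustration, treat UCR as normal in the cohort, linearly related to Bayley score, and cut to its top 20%. The variance of UCR falls to v = 0.219 of its cohort value, and a cohort correlation r becomes r√v / √(1 − r² + r²v). Cohort values of 0.1, 0.2, 0.3, 0.4 and 0.5 leave about 0.05, 0.10, 0.15, 0.20 and 0.26 within the trial. By the formula in step 2, power is then 80.6%, 80.9%, 81.3%, 82.1% and 83.2%.

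5. *Chance imbalance.* The between-arm difference in mean UCR has a 95% range of ±1.96 × √(2/74) = ±0.32 SD of UCR. An imbalance at that limit moves the unadjusted Bayley difference by 0.32 × 15 × r, which is about 0.5, 1.0 or 1.4 points for r = 0.1, 0.2 or 0.3, against a target of 7.

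**The case against.** The strongest case against is that nothing here is wrong. The model is valid, the sample size assumes no help from covariates, and omitting a prognostic variable from a randomised linear comparison neither biases the estimate nor distorts the type I error. Choosing further covariates is also commonly left to the SAP, which is not shown. All of this stands, and it is why the point is an optional improvement.

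It also stands that the evidence for UCR as a covariate is indirect. The Abstract speaks of an abnormal UCR and of poor outcomes in general. It does not say that the degree of abnormality above 0.8 predicts Bayley score at 2 years. All randomised women are abnormal by that definition, and the section on operational issues acknowledges observer variability in Doppler measurement, which would weaken any remaining gradient.

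A reader might infer four stronger things that the article does not support:

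- *That precision is certainly being lost.* No UCR–Bayley correlation is given, and adjustment can cost slightly more than it returns when r is below about 0.08.
- *That the trial has no margin.* The 185 allows for 20% loss, while section {20a} expects up to 15% of long-term outcomes to be missing. At 15%, 185 × 0.85 gives about 157 children analysed and about 83% power unadjusted.
- *That chance imbalance in UCR biases the result.* It does not over repeated trials, and the confidence interval already allows for it. Adjustment only removes that part of the noise.
- *That much larger gains are available.* If added predictors explained 10% or 20% of Bayley variance, power would be 84.4% or 88.4%. That would probably need variables such as child sex or socioeconomic status. The article does not describe collecting socioeconomic status; the term appears only in the abbreviation list, which is no proof of collection.

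What survives is that the stated adjustment set can be improved with a value every randomised woman already has, at almost no cost.

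**Conclusion.** The point holds as a low-priority efficiency suggestion. The primary model as written omits the continuous UCR at randomisation, a pre-allocation measurement available for all randomised women. Including it would take power from 80.5% to about 80.9–84.0% if the within-trial correlation lies between 0.1 and 0.3. Under the truncation illustration, even a cohort correlation of 0.5 adds less than 3 percentage points. It would also remove a chance shift of up to about 0.5–1.4 points over the same range of r. These sizes rest on an assumed correlation, a two-sided test, a linear relation and, for the truncation step, a normal UCR. The planned analysis remains valid and meets its stated power, and the omission should not be reported as a flaw in the trial.

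**What to change.** Before unblinding, amend the primary-analysis wording so that the linear model includes the confirmatory UCR at randomisation as a continuous covariate, alongside the stratification factors. The current sentence uses the singular while section {16a} lists two, so the amendment should name which ones enter. Add other pre-randomisation or fixed predictors, such as child sex, only if the CRF records them. Report the model with stratification factors only as a sensitivity analysis.

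For UCR this needs no new measurement. Each covariate costs one degree of freedom and, if it proves uninformative, a negligible loss of precision (about 0.3 percentage points of power for UCR at r = 0). Data analysts are blinded under section {17a}, so the choice can still be fixed without knowledge of the results.

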### Interim analyses {21b}

A safety interim review is planned after the pregnancy outcomes of 80 RCT patients have become available without the use of inferential statistics. Hence, statistical stopping rules are not applied and correction for alpha spending is not required. Only the members of the DSMB and an independent statistician who conducts the interim review will have access to the data and reports. Given that the efficacy endpoint cannot be determined before the age of 2 years, interim analysis for efficacy is not feasible and will not be conducted.

### Methods for additional analyses (e.g., subgroup analyses) {20b}

#### Biomarker analyses

There will be subgroup analysis and biomarker analysis to evaluate the effect of early delivery on the abovementioned outcome measures in subgroups defined by (a) an abnormal or normal serum level of placenta growth factor (PlGF), (b) gestational age categories, (c) other patient characteristics available at baseline such as gestational age and estimated fetal weight, and (d) the different components of UCR (MCA, UmbA). Given the chance of spurious findings with multiple testing in a limited sample size, these analyses will be primarily hypothesis-generating and significance will be determined after Bonferroni correction.

#### Cost-effectivenesss analysis (CEA)

A trial-based cost-effectiveness analysis (CEA) will be performed, based on empirical data obtained in the RCT and a matched subgroup of the cohort. The CEA will be performed from the healthcare and societal perspective, using costs generated both within and outside of the healthcare sector. The time horizon of data collection for the economic evaluation will be 24 months, corresponding to the follow-up time and covering the neonatal care period and possible events following the neonatal period. As the intervention will mainly have a large impact on cost-effectiveness by a lifelong increase in quality-adjusted life years (QALYs) and saving of costs through improved neurological development, as measured by the Bailey-III score, we will estimate this by linking this improvement to use of healthcare resources and utility of these infants in later life by using medical literature [26, 27]. Similarly, women who have undergone a cesarean section may experience disutilities and additional costs in later life due to repeat cesarean sections. These healthcare effects and costs will also be estimated, but as with the infants, cannot be estimated directly from this trial.

The volume of health care consumption will be measured using an adapted version of the iMCQ, which the participants of the RCT and a matched subgroup of the cohort are asked to complete 24 months after delivery. This questionnaire will measure healthcare utilization for both in-hospital as well as out-of-hospital medical expenses, which include but are not limited to: medication, days in the hospital, outpatient visits after discharge, visits to the general practitioner, psychological guidance, and use of alternative medicine. Unit costs will be derived from tariffs as described in the “Zorginstituut Nederland Kostenhandleiding.” Medication costs will be derived from the “Zorginstituut Nederland Medicijnkosten” [28, 29]. If dosages are lacking in the iMCQ, standard dosages will be derived from the “Zorginstituut Nederland Farmacotherapeutisch Kompas” (WHO DDDs). In the case of uncertainty about the type of medication used by an individual, the most likely type of medication will be used. The iPCQ will be used to derive losses in productivity for the calculation of cost-effectiveness from a societal perspective. Travel costs per individual will be calculated using average travel distances and standard tariffs from the “Zorginstituut Nederland Kostenhandleiding” in combination with the number of visits to a specific medical facility as denoted by the participants in the iMCQ.

Health-related quality of life will be measured using the EQ5D-5L Questionnaire provided to women who have entered the trial at baseline, 6 weeks, 12 months, and 24 months after delivery. In the case of missing data on either costs or effects, these will be imputed by using multiple imputation techniques. The prevalence of any relevant outcomes in neonates will be extracted from CRF registration forms and electronic health records at the end of the trial. The utility scores related to these outcomes will be derived from relevant scientific literature for the calculation of cost-effectiveness. After completion of data collection, the incremental cost-effectiveness ratio (ICER) will be calculated by dividing the difference in costs between usual care and the intervention by the difference in QALYs between usual care and intervention. ICERs will be calculated for mothers and children separately and combined to analyze the potential differences in cost-effectiveness. Sensitivity analysis will be performed on parameters, which are expected to have the largest uncertainty. Bootstrapping will be used to determine the uncertainty surrounding the ICERs. The results from the bootstrap analysis will be used for plotting a cost-effectiveness acceptability curve to demonstrate the probability that the intervention strategy will be cost-effective compared to current practice when using a range of cost-effectiveness thresholds. Cost-effectiveness planes will be created to graphically represent the results from the bootstrap analysis.

#### Budget impact analysis (BIA)

A budget impact analysis (BIA) will be performed alongside the RCT to estimate the financial consequences of UCR/CPR-based delivery in women with a fetus suspected of FGR. If our study reveals that this strategy care has favorable cost-effectiveness, or is cost-saving while not reducing health outcomes, compared to standard care of intensive monitoring, the BIA will estimate the financial consequences of changing the standard care strategy from usual care to inducing delivery from gestational age more than 36 weeks in women with fetuses identified as mild SGA (EFW/FAC p3–p10) and more than 34 weeks (EFW/FAC below p3). Budget impact concerning the mother will not be very large, with an annual number of ~ 4350 patients. However, it should be considered that this is a dominant strategy, and the largest impact will be on the cost savings for these newborns in later life. Estimates for cost savings presented in the anticipated cost-effectiveness are very conservative as for the infants clinically improved Bayley-III score, corresponding to improved neurologic development, will require less resource use concerning, e.g., motor therapy [26, 29]. While the incidence of more severe neurodevelopmental morbidities, such as cerebral palsy, will be low, their health care burden is expected to be very large, partially due to their life span. The aim of the BIA is to study the costs of different scenarios for the nationwide introduction of UCR/CPR-based delivery in women with SGA fetuses. The BIA will have a simple design, consisting of a linear extrapolation of evidence collected in this project. The BIA will be performed with a time horizon of 5 years and split into results for all 5 years to demonstrate whether there turn-on-investments improve over time. BIA results will be reported separately for each year within the time horizon, and indexation will be applied. Discounting of results will not be necessary according to BIA guidelines that will be followed throughout our BIA study [30].

#### Methods in analysis to handle protocol non-adherence and any statistical methods to handle missing data {20c}

Patients who withdraw from the study will remain in their treatment group for the intent-to-treat analysis. Every effort will be made to obtain complete information on each patient randomized. The only reason for not obtaining complete information is that the patient was lost to follow-up or that she withdraws consent to access her medical chart after delivery. Once a woman has been randomized, even if she refuses the study intervention for any reason, follow-up will be continued including planned visits and maternal and fetal surveillance. Her data will be considered as per intention-to-treat in the final analysis. Imputation of outcome data will not be applied.

#### Plans to give access to the full protocol, participant-level data, and statistical code {31c}

Manuscripts resulting from this trial will be submitted to open access journals dedicated to this topic, or conventional journals providing Open Access as an option for individual publications. Original data will be made available upon request for re-use in future studies after the publication of the results.

### Oversight and monitoring

#### Composition of the coordinating center and trial steering committee {5d}

The sponsor in the coordinating center has established a working group overseeing the trial and its procedures. Procedural management is in the hands of the NVOG Consortium clinical trials unit.

